### Consent and ethics

This project has been approved by the university Human Research Ethics Committee. All participating aged care staff and aged care residents will be provided with a plain language statement and will be asked to provide written informed consent to participate. For staff, the consent will be to participate in the staff training and/or questionnaire completion. For residents, the consent will be sought to access their records at the facility to obtain health-related information and collect self-reported quality of life assessments. If residents are unable to provide consent (e.g. due to impaired cognitive function), consent will be sought from their next of kin. There will be no reimbursement for residents or staff participating in the study.

### Participants

A total of 834 staff (22 in each facility) will participate in the study. In order to be eligible to participate in the study, staff members will have to be a full-time, part-time, or casual permanent employee at the facility, and be either a member of the senior or general staff. Approximately equal numbers of senior (e.g. registered nurse) and general (e.g. personal care attendant) staff across a range of roles will be recruited at each RACF. Staff employed on a contractual basis from an external organization will not be permitted to take part in the study.

A total of 744 residents (20 in each facility) will also be recruited to participate in the study. Residents will be eligible to participate in the study if they: (a) have lived in the facility for longer than 3 months; (b) can effectively communicate in English; (c) are not considered to have a severe cognitive impairment, based on their most recent Psychogeriatric Assessment Scale (PAS) score [21]; (d) are aged 65 years and older; and (e) are physically able to participate. After potential participants have been identified by the facilities, they will be approached by a member of the research team with an invitation to take part in the study.

### Intervention program

The translation strategy utilized in the RCC used the Dementia Training 4-stage ‘Awareness-Agreement-Adoption-Adherence’ approach to designing continuing education for health professionals [19]. The first session is designed to engage the senior staff only, orienting them to the program scope and goals, and their critical role as leaders during the training program and beyond. It aims to clarify the key CDC principles and how they relate to residential aged care. The key factors that may pose a challenge or help facilitate the successful implementation and sustainability of CDC will be explored, along with the key organizational factors (i.e. staff autonomy and recognition; workplace fairness and innovation; trust; support and cohesion). Senior staff will also be introduced to tools such as the Resident Care Form, which will be used to foster the collaborative working relationship between care staff and residents. The Resident Care Form will be used to elicit resident choices on a range of areas of care (e.g., meals, time for showers, activities, etc.). This session also discusses the importance of leadership in facilitating change, specifically transformational leadership. Senior staff will then be encouraged to adopt a transformational leadership style when guiding the participation of other staff members in the remainder of the program.

Sessions 2 to 5 will involve both senior and general staff. Sessions 2 and 3 will review the philosophy and approach of CDC, and explore staff members’ prior knowledge, ideas and experiences of CDC. The importance of building and maintaining working relationships with residents will be emphasized. The Resident Care Form will be introduced to general staff as a tool to support residents’ choice and control over their care decisions. In these sessions, senior and general staff will also discuss the factors that may hinder or promote successful implementation and sustainability of CDC.

There will be a 4-week break from training between Sessions 3 and 4, in which care staff will complete the Resident Care Forms with residents and practice implementing any changes requested by residents in their activities. During this time, facilities that have been allocated to Condition 1 (the RCC Program plus support) will also receive weekly support from a member of the research team to assist them to address any barriers and foster enablers to the implementation of CDC. The study champion will also assist in this process. Following the training break, staff members will be asked to review their experience with the Resident Care Form, and draw on learnings from previous sessions to develop a CDC implementation plan during Sessions 4 and 5. Following the end of the training program, the staff at sites allocated to Condition 1 (the RCC Program plus support) will receive a further 12 weeks of support to implement their CDC plans for one day a week.

### Evaluation of the training program

#### Evaluation measures for aged care residents

The following measures will be completed by the residents at baseline and 3 months, 6 months, and 12 months follow-up. A research assistant who is blind to the condition will individually sit with each resident and work through the measures listed below.

#### Quality of life

Residents’ self-reported QoL will be assessed using the Quality of Life – Alzheimer’s Disease (QoL-AD) Aged Care Adaptation questionnaire [22]. Residents will rate 15 different aspects of their life (e.g. physical health, mood, memory, functional ability, interpersonal relationships and engagement in meaningful activities) on a 4-point scale from ‘Poor’ to ‘Excellent’. Higher scores indicate higher quality of life (possible range: 0 to 60). Previous research on this scale has demonstrated high reliability (α = .92) [22].

#### Residents’ choice and control

The Duncan Choice Index [23] will be used to assess residents’ perception on the amount of choice available to them in leisure and self-care activities. The scale consists of 28 quantitative items that will be categorized under headings, including Eating, Grooming, and Leisure. Responses are recorded on a 3-point scale: ‘Never’, ‘Sometimes, and ‘Always’, with higher scores indicating a higher frequency of choice opportunities (possible range: 28–84). Each category will include an open-ended question that inquires whether the resident would like to have more choice in that particular area. The scale was reported to have a Cronbach’s alpha of .84 [23].

#### Working relationship

Residents’ perceptions of the extent to which their care staff support their autonomy will be assessed using Perceived Autonomy Support: The Health Care Climate Questionnaire [24]. This scale contains 15 items, which will be adapted to suit the residential aged care setting. Responses are recorded on a 3-point scale, with higher scores indicating a more positive perception of support to the resident’s autonomy (possible range: 15 to 45). Previous research on this scale has demonstrated high reliability (α = .92) [24].

#### Evaluation measures for aged care staff

The following measures will be completed by care staff at all residential facilities at baseline, post-intervention and 3 months, 6 months, and 12 months follow-up.

#### Transformational leadership

The Multifactor Leadership Questionnaire (MLQ) – Leader version by Bass and Avolio [25] will be used to assess the senior staff’s perception of their own leadership style. The scale consists of 45 items in 9 subscales that can be condensed into 4 subscales. Responses are recorded on a 5-point scale, with higher scores on each subscale indicating the extent to which a staff member employs a particular leadership style. The scale has demonstrated good reliability, with the alpha for the subscales ranging from .61 to .91 [25].

#### Job satisfaction

An 8-item questionnaire drawn from Tate, Whately, and Clugston [26] will be used to measure the costs and rewards associated with an individual’s job. Staff will respond on a 5-point Likert scale, with higher scores indicating greater job satisfaction (possible range: 8 to 40). The scale has been reported to have good reliability (α = .85) [26].

#### Intention to quit

Staff members will respond to two questions from Tate et al. [26] to rate their intention and likelihood to leave their current job. Responses are provided on a 5-point scale, with higher scores indicating a greater intention to quit (possible range: 2 to 10). Previous research has demonstrated acceptable reliability for this scale (α = .61) [26].

#### Working relationship

Staff members’ perception of their relationships with residents will be assessed using the Scale to Assess Therapeutic Relationships in Community Health Care, Clinician version (STAR-C) [27]. The scale contains 12 items, which will be adapted to better suit the residential aged care setting and sample population. Staff members will respond using a 5-point Likert Scale, with a higher total score indicating a more positive working relationship (possible range: 0 to 44). The scale has been reported to have acceptable test-retest reliability (*r* = .92) [27].

#### Experience of CDC

The Individualized Care Scale by Chappell and colleagues [28] will be used to measure staff members’ perception on the extent to which principles of CDC are already practiced in their facility. The scale consists of four sub-scales. *Knowing the Person* (α = .77) measures staff members’ perception of how well they know the resident they are caring for as a person. It contains 13 items, and responses are recorded using a 4-point scale. Higher scores indicate that carers believe they know the residents well (possible range: 13–52). *Resident Autonomy* (α = .80) contains 8 items which assess staff members’ perception of how much control and choice the residents have in their everyday environment and activities that are related to their care. This scale uses a 5-point scale, with higher scores indicating a belief that the facility in which the staff member is employed supports the residents’ autonomy (possible range: 8–40). *Staff-to-resident Communication* (α = .64) refers to the extent to which care staff use communication that is not task-focused and communicate with residents about the residents’ care needs and preferences. Responses to the 7 items in this subscale are recorded on a 4-point scale, with higher scores describing a lower frequency of task-focused forms of communication between staff and residents (possible range: 7–28). *Staff-to-staff Communication* (α = .76) measures how actively staff members communicate with one another about residents’ needs and preferences and about facility procedures and practices. Responses to the 11 items in these subscales are recorded on a 4-point scale, with higher scores indicating more frequent exchange of information among staff members regarding resident care (possible range: 11–44).

Additionally, staff opinions about potential advantages and disadvantages of the CDC approach will be assessed using 6 open ended questions. The questions will only be completed by staff in Condition 1 and 2, following Session 3 of the training program (when staff are familiar with CDC) and at 6-month follow-up. These questions will be used to determine if their understanding and perception of CDC has altered following the implementation of CDC strategies in the facility.

#### Work role stress

The Strain in Dementia Care Scale [29] will be used to assess the extent to which care staff members experience stress while caring for residents. The scale consists of 27 items which ask staff to indicate how often they experience a stressful situation, thought, or feeling in their role as a carer, and how much stress it causes them when it occurs. Responses are recorded on a 4-point scale, with higher scores indicating a higher frequency of the occurrence and higher stress (possible range: 27–108). The scale has been reported to have satisfactory internal consistency (α = .89) [29].

#### Person-centered care

The Person-centered Care Assessment Tool (P-CAT) will be used to measure the extent to which the care within a facility is experienced by staff as being person-centered [30]. The scale contains 13 items. Responses are recorded on a 5-point scale, with higher scores indicating the staff member’s perception that the care approach within their facility adheres to person-centered care approaches (possible range: 13–65). Previous research using the scale has reported good reliability (α = .84) [30].

#### Staff perceptions of organizational climate

This construct will be measured using the Organizational Climate Questionnaire (OCQ) [15]. The scale consists of eight subscales that constitute organizational climate: trust, autonomy, fairness, innovation, pressure, cohesion, support, and recognition. Each of these subscales contains 5 questions and has good reliability (α > .80) [15]. Responses are recorded on a 5-point scale, with higher scores indicating a more positive perception of the organizational climate (possible range: 40 to 200).

#### Readiness for organizational change

This four-factor 25-item scale measures current perceptions of the organization [31]. Responses are recorded on a 5-point scale. Coefficient alphas for the four factors were .94 for *Appropriateness*, .66 for *Personally Beneficial*, .87 for *Management Support* and .82 for *Change Efficacy* [31]. This scale will only be completed after Session 3 of the training program and at 6-month follow-up to determine if the organization’s readiness to change has altered due to the implementation of the program and practice in CDC strategies.

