**Methods:**

The study will adopt a cluster randomized controlled design with 39 facilities randomly allocated to one of three conditions: delivery of the RCC program plus additional organizational support, delivery of the program without additional support, and care as usual. A total of 834 staff (22 in each facility, half senior, half general staff) as well as 744 residents (20 in each facility) will be recruited to participate in the study. The RCC program comprises five sessions spread over nine weeks: Session 1 clarifies CDC principles; Sessions 2 to 5 focus on skills to build and maintain working relationships with residents, as well as identifying organizational barriers and facilitators regarding the implementation of CDC. The primary outcome measure is resident quality of life. Secondary outcome measures are resident measures of choice and control, the working relationship between resident and staff; staff reports of transformational leadership, job satisfaction, intention to quit, experience of CDC, work role stress, organizational climate, and organizational readiness for change. All measures will be completed at four time points: pre-intervention, 3-months, 6-months, and 12-month follow-up. Primary analyses will be conducted on an intention to treat basis. Outcomes for the three conditions will be compared with multilevel linear regression modelling.

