### Hypotheses and expected outcomes

It is hypothesized that, relative to care as usual, the RCC Program will improve residents’ QoL (Primary Outcome Measure – QoL at 6-months follow-up); their perceptions of their level of choice and control and the working relationship with staff (Secondary Outcome Measures). It is also hypothesized that the RCC Program will lead to organizational change; improve staff perceptions of their use of transformational leadership, job satisfactions, working relationship with residents, experience of CDC; reduce their job stress and intention to quit (Secondary Outcome Measures). Supplementing the RCC Program with extra support to assist staff to address barriers to CDC implementation and so implement change is hypothesized to lead to greater benefits than the same program without this support. These changes are predicted to occur, relative to baseline at 3-months, 6-months, and 12-months follow-up.

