## Methods/design

### Study design

A cluster randomized controlled trial design will be employed in this study, with 39 facilities randomly allocated to one of three conditions (13 facilities in each). Each of the 13 aged care organizations will provide three separate facilities to take part in the study, which will then be randomly allocated to one of the three conditions. Allocations of facilities will be completed by the biostatistician not involved in data collection using random numbers generated at random.org.

The first condition will involve the delivery of the five-session RCC Program plus additional organizational support. This organizational support is designed to assist staff to implement the CDC model of care within their facility. It will be provided one day a week for four weeks following Session 3 and a further one day a week for 12 weeks following Session 5. This training is above and beyond what is provided within each session of the training program, and is designed to assist staff in applying their learnings from the program (in line with the facility’s CDC implementation plan) and assist the staff to work through challenges as they arise. Sessions 4 and 5 will occur immediately after a four-week gap (see Fig. 1). The second condition will be a second intervention group, where staff will be provided with the RCC Program without the additional organizational support. The third condition will be a ‘care as usual’ control group. Staff will be provided with paid release time to attend the program. Data from the residents will be collected by a research assistant who is blind to the condition to which the facility is allocated.

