### Statistical analysis

Primary analyses will be on an intention to treat basis, with supplementary ‘per protocol’ analyses (at least 75% of staff enrolled in the study completing at least 75% of training sessions). To account for the within-facility clustering and repeated assessments of staff and residents, hypothesized main effects for outcomes will be tested using a multilevel linear (or generalized linear, where appropriate) regression modelling. For each outcome, a separate three-level regression model will be specified, with repeated measurements as level 1, individuals as level 2, and facility as level 3. The regression models will include Condition allocation, assessment time point, and Condition by time interaction as predictors. Facilities and individuals will be modelled as random effects with remaining variables modelled as fixed effects. Missing data will be handled with conditional maximum likelihood estimation. The impact of possible non-random attrition will be explored with simulation analyses.

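### Readiness for change is first measured after Session 3, with no defined reading in usual-care facilities at that point, so its change due to the program versus usual care cannot be estimated as planned

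*Protocol article*

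**What the plan says.** The abstract's Methods paragraph ends its list of staff secondary outcomes with "work role stress, organizational climate, and organizational readiness for change", and then gives one schedule for everything: "All measures will be completed at four time points: pre-intervention, 3-months, 6-months, and 12-month follow-up". The section on evaluation measures for aged care staff introduces its instruments, this scale among them, as "completed by care staff at all residential facilities at baseline, post-intervention and 3 months, 6 months, and 12 months follow-up".

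The section on readiness for organizational change departs from both: "This scale will only be completed after Session 3 of the training program and at 6-month follow-up". It gives the purpose as "to determine if the organization’s readiness to change has altered due to the implementation of the program and practice in CDC strategies".

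Three other sections bear on this:

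- Hypotheses and expected outcomes sets the reference point for change: "These changes are predicted to occur, relative to baseline at 3-months, 6-months, and 12-months follow-up".
- Study design defines the comparator: "The third condition will be a ‘care as usual’ control group".
- Statistical analysis specifies a separate three-level model for every outcome, with no exception for this scale: "The regression models will include Condition allocation, assessment time point, and Condition by time interaction as predictors".

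**The concern.** The stated purpose is causal: has the program changed readiness? That needs either a value from before the program, or a randomized comparison with facilities that did not receive it. The two occasions named do not supply the first and do not clearly supply the second.

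By the first reading, senior staff have attended Sessions 1 to 3 and general staff Sessions 2 and 3. The intervention section says these sessions deal with leadership for change, with organizational factors, and with what helps or hinders the adoption of consumer directed care. That content bears directly on readiness, so the first reading is a post-treatment value. Usual-care facilities have no Session 3, and the article gives no matching date for them.

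The practical risk is that the rise or fall from Session 3 to 6 months in trained facilities is reported as the effect of the program. It would omit whatever the first three sessions did. Without a control reading on the first occasion, it would also include any general drift over the same months.

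**Working it through.** **1. The schedules side by side**

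| Section | Occasions | Facilities |
|---|---|---|
| Abstract, Methods | Pre-intervention, 3, 6, 12 months | Not restricted |
| Evaluation measures for aged care staff | Baseline, post-intervention, 3, 6, 12 months | All |
| Hypotheses and expected outcomes | Change from baseline at 3, 6, 12 months | Against usual care |
| Readiness for organizational change | After Session 3, and 6 months, only | Not stated |

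Only the 6-month occasion is common to all four rows. The readiness section has no baseline.

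**2. What each comparison estimates**

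Let D be the effect of the program on readiness at 6 months, f the share of D already present after Session 3, and T the drift between the two readings that would occur without the program.

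- Trained arms alone, 6 months minus after Session 3: T + (1 − f)D.
- The same change minus a calendar-matched control change, if one existed: (1 − f)D.
- All three arms at 6 months only: D, because facilities were randomized.
- All three arms at 6 months, adjusted for a pre-training value: D, usually with better precision.

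The share captured by the second contrast is 75% at f = 0.25, 50% at f = 0.5 and 25% at f = 0.75. If an early gain fades, f exceeds 1 and the change takes the wrong sign.

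**3. The plan's staff sample size**

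The inputs, from Study design, are d = 0.35, 80% power, two-sided 5%, intra-class correlation 0.02, 22 staff per site and 33% attrition.

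- Per arm without clustering: 2 × (1.96 + 0.8416)² / 0.35² = 128.1, so 129.
- Design effect: 1 + (22 − 1) × 0.02 = 1.42. Then 129 × 1.42 = 183.2, so 184.
- Attrition: 184 / 0.67 = 274.6, so 275 per condition, against 278 stated. With 23 per site the result is exactly 278.

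The staff number is therefore sound, and no arithmetic in the plan is in dispute.

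**4. What the late first reading costs**

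Effective number per arm: 278 × 0.67 / 1.42 = 131. For correlation ρ between the two readings, the SD of the change is √(2(1 − ρ)), which is 1 at ρ = 0.5. Power is Φ((1 − f) × 0.35 × √(131.17/2) / SD − 1.96), with √(131.17/2) = 8.10. This grants a matched control reading, which the article does not define, and applies the same design effect to the change.

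| f (assumed) | Contrast | Power, ρ = 0.3 | ρ = 0.5 | ρ = 0.7 |
|---|---|---|---|---|
| 0 | 0.35 | 66.8% | 80.9% | 95.5% |
| 0.25 | 0.2625 | 43.5% | 56.6% | 78.4% |
| 0.5 | 0.175 | 22.3% | 29.4% | 44.8% |
| 0.75 | 0.0875 | 8.7% | 10.5% | 14.8% |

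A three-arm comparison at 6 months alone has 80.9% power for a pairwise d of 0.35, whatever f is (0.35 × 8.10 − 1.96 = 0.87; Φ = 0.81). The article gives neither f nor ρ, so the table is an illustration.

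**The case against.** A reader might infer that control facilities never complete the scale, and that the trial therefore has no randomized estimate for this outcome and leaves drift wholly uncorrected. The article does not support that, for two reasons.

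- The readiness section restricts timing and is silent on conditions, while the staff-measures section covers all facilities. Where the authors limit an instrument to the trained arms, as with the open-ended questions under Experience of CDC, they say so. If controls complete the scale at 6 months, the randomized comparison at that time is valid without a baseline.
- Conditions 1 and 2 receive the same program up to Session 3. The added organizational support begins after that session (Study design and Intervention program). A reading taken before the support starts is a proper starting value for Condition 1 versus Condition 2. That contrast is one of the stated hypotheses, it is randomized and concurrent, and it removes drift.

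The timing may also be deliberate. Practice of the new approach begins in the four-week break after Session 3, and the open-ended questions are placed there because staff by then know the model. Readiness asked about a change that staff do not yet understand may be harder to interpret. The abstract's schedule is plainly a summary, since it also omits the staff post-intervention reading, so its conflict with the readiness section carries little weight alone.

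All of this stands, and it narrows the point. It does not supply a pre-training value, a control reading matching the first occasion, or an exception in the analysis section. The readiness section gives no familiarity rationale of its own, and it describes the scale as measuring current perceptions of the organization, which staff can report at baseline.

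**Conclusion.** The point holds for the comparison that the readiness section itself announces. As written, the change due to the program versus usual care cannot be estimated for this scale, and neither can the Condition by time term against control. The effect of Sessions 1 to 3 sits in the starting value. The four sections on timing also disagree and must be reconciled.

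It does not hold as a statement that the outcome yields nothing. The added-support contrast survives if the first reading precedes the support. The 6-month comparison of all three arms survives if controls complete the scale then, which the article neither excludes nor states.

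The size depends on f. At an assumed f of 0.5 the change contrast is halved to 0.175, and power is about 22% to 45% for ρ from 0.3 to 0.7. If nothing has changed by Session 3 (f = 0), nothing is lost from this source, but a control reading would still be needed. The consequence is limited to one of several staff secondary outcomes. Resident quality of life, the primary outcome, is untouched. The amendment is worth making because it is cheap.

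**What to change.** - Add the 25-item scale to the baseline questionnaire that staff in all three conditions already complete, and state that all three conditions complete it again at 6 months.
- Analyse the 6-month difference between conditions, adjusted for baseline, within the planned multilevel framework.
- Keep the post-Session 3 reading in Conditions 1 and 2 as the starting value for the added-support contrast, and state that it is taken before the support begins.
- For rounds whose baseline has passed, compare the three arms at 6 months only. Do not describe within-arm change from Session 3 as the effect of the program.
- Align the abstract, the hypotheses, the introduction to the staff measures and the readiness section, and name this scale's occasions in the analysis section.

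Study design has data collection starting in May 2018 and roll-out running to July 2019. The article appeared in November 2018, so later rounds could still have gained a baseline at that time.

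The cost is a slightly longer baseline questionnaire and a minor amendment. Some staff will know less about consumer directed care at baseline, which may make that reading noisier as a covariate. It does not bias the randomized 6-month comparison.
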